## Abstract

**Introduction:**

The risk of major bleeding complications in catheter directed thrombolysis (CDT) for acute limb ischemia (ALI) remains high, with reported major bleeding complication rates in up to 1 in every 10 treated patients. Fibrinogen was the only predictive marker used for bleeding complications in CDT, despite the lack of high quality evidence to support this. Therefore, recent international guidelines recommend against the use of fibrinogen during CDT. However, no alternative biomarkers exist to effectively predict CDT-related bleeding complications. The aim of the POCHET biobank is to prospectively assess the rate and etiology of bleeding complications during CDT and to provide a biobank of blood samples to investigate potential novel biomarkers to predict bleeding complications during CDT.

**Methods:**

The POCHET biobank is a multicentre prospective biobank. After informed consent, all consecutive patients with lower extremity ALI eligible for CDT are included. All patients are treated according to a predefined standard operating procedure which is aligned in all participating centres. Baseline and follow-up data are collected. Prior to CDT and subsequently every six hours, venous blood samples are obtained and stored in the biobank for future analyses. The primary outcome is the occurrence of non-access related major bleeding complications, which is assessed by an independent adjudication committee. Secondary outcomes are non-major bleeding complications and other CDT related complications. Proposed biomarkers to be investigated include fibrinogen, to end the debate on its usefulness, anti-plasmin and D-Dimer.

**Discussion and conclusion:**

The POCHET biobank provides contemporary data and outcomes of patients during CDT for ALI, coupled with their blood samples taken prior and during CDT. Thereby, the POCHET biobank is a real world monitor on biomarkers during CDT, supporting a broad spectrum of future research for the identification of patients at high risk for bleeding complications during CDT and to identify new biomarkers to enhance safety in CDT treatment.

## Introduction

Acute limb ischemia (ALI) is a potentially lethal condition in which the viability of the limb is threatened due to an acute decrease in limb perfusion [1]. Following the Rutherford classification for ALI [2], catheter directed thrombolysis (CDT) is generally the preferred treatment strategy in viable (Rutherford I) or marginally threatened (Rutherford IIa) ALI [1]. The benefit of CDT should be counterbalanced with the inherent associated risk of bleeding complications which remain a major concern when applying CDT. Bleeding complications rates range from 11% to 56%, with an average complication rate of 18% with almost half of these being major [3]. One of the most severe CDT related major complication is haemorrhagic stroke, which may occur in up to 4% of patients undergoing CDT for ALI [4].

Periprocedural prediction of bleeding complications during CDT has been topic of research since long.

Standard operating procedures (SOP) of CDT for ALI are heterogeneous, which makes it challenging to compare results of previous single centre cohort studies [3,5]. This heterogeneity is not caused by negligence, but by a lack of research on the best treatment standards for CDT, as most SOP are still based on landmark trials like the ‘Surgery versus Thrombolysis for Ischemia of the Lower Extremity’ (STILE, 1994) trial and the ‘Thrombolysis Or Peripheral Arterial Surgery’ (TOPAS, 1998) trial [6,7]. These studies have been performed nearly thirty years ago and included patients are likely not representable for the current CDT-population. Duration of ALI for STILE inclusions was up to 6 months and patients enrolled in the TOPAS trial were treated with intravenous heparin up to two times the baseline level of activated partial thromboplastin time (aPTT) plus intra-arterially CDT, causing a high rate major bleeding complications. Despite the heterogeneity in SOP, plasma fibrinogen level (PFL) monitoring has been widely used to predict the occurrence of major bleeding complications, as depicted by a recent survey among physician members of the Society of Interventional Radiology [8]. This practice is mainly based on the observed association between low PFL and the occurrence of major bleeding complications in the STILE trial, although PFL measurement in this study was done only after CDT [6]. Furthermore, a recent systematic review described the predictive value of PFL for major bleeding during CDT and stated that it could not be clarified for which threshold PFL is associated with haemorrhagic complications. Moreover, the role of PFL, in general, as predictor for haemorrhagic complications during CDT remains unproven [9]. Currently, the European Society for Vascular Surgery (ESVS) guidelines on ALI do not recommend routine monitoring of PFL during thrombolysis, mainly due to the lack of high quality evidence underlying its practice [1]. This finding advocates the necessity to prospectively investigate the predictive value of PFL, as well as a need for identification of other potential predictors.

The aim of POCHET biobank (**P**redictors **O**f bleeding **C**omplications during cat**H**eter dir**E**cted **T**hrombolysis for peripheral arterial occlusions) is to prospectively collect data of ALI patients treated with CDT to assess the rate and etiology of bleeding complications during CDT and to establish a prospective biobank of blood samples taken prior and during CDT to investigate current and potential new biomarkers that predict bleeding complications.

## Methods and design

### Study design

The POCHET biobank is a multicentre prospective biobank study including all consecutive patients eligible for CDT for the treatment of ALI of the lower limb. All patients are treated according to the standard operating procedure for CDT which is aligned in each participating centre. Patients are treated with either Urokinase or Alteplase, as effects and risks are similar [10]. Results will be corrected for thrombolytic medication given. The standard operating procedure is further elaborated in the (S1 File) Written informed consent is collected and included patients donate venous blood samples prior to CDT and simultaneous to standard blood collection every six hours for the duration of thrombolysis. With a maximum CDT-duration of 72 hours, the number of blood collections are maximised at 13 times. As the nature of this study is an observational biobank study, registration as a clinical trial is not applicable [11].

### Ethical approval

This biobank is conducted with approval of the Biobank Research Ethics Committee (BREC) of the University Medical Center (UMC) Utrecht (approval number 19–731, date of approval 30 march 2021). Within this ethical approval, donating a maximum of 136.5 ml blood to the biobank is considered safe and does not affect standard healthcare [12]. For all participating hospitals, a transfer of human material and associated personal data agreement is signed in order to store all collected samples in the central biobank in the UMC Utrecht, the Netherlands. Before plasma samples and its corresponding clinical data can be analysed for a specific research question, approval of the BREC is necessary.

### Inclusion and exclusion criteria

When the treating physician decides CDT is the treatment of choice for ALI, patients must fulfil the following inclusion criteria for the POCHET study:

Subacute (<6 weeks) thrombotic occlusion of a native artery, bypass or stent in the iliac or femorodistal artery.18 years of age.Written informed consent.

### Exclusion criteria

A patient is not able to participate in this biobank study if one of the following criteria is present:

No treatment indication for CDTNot willing to or not able to provide written informed consentAbsolute or relative contra-indication for thrombolytic therapy (see S1 File)

### Treatment location

In all participating centres, a dedicated angio suite is used for all angiograms made throughout the CDT process: for confirmation of the occlusion, for (mechanical) thrombectomy prior to CDT if deemed necessary and for evaluation of CDT treatment. Patients are being monitored in at least a medical care unit facility during CDT (See S1 File, sub 4, 7 and 9).

### Sample size

The POCHET biobank is an ongoing biobank storing blood samples of patients undergoing thrombolytic therapy for future biomarker research questions. As knowledge develops on predicting biomarkers on bleeding complications during CDT, new research questions are likely to arise constantly. As such, a sample size calculation on a biobank is not possible. The first blood sample assessments on bleeding biomarkers will be done at 100 inclusions. Currently, POCHET biobank has approval for 500 participants, but is likely to expand after the first biomarkers on bleeding complications are explored and higher statistical power might be needed. For this, it is anticipated that the POCHET biobank will become the biggest cohort of plasma samples of patients which are treated with CDT for ALI.

### Endpoint definitions

The primary endpoint is the occurrence of non-acces site related major bleeding during CDT. Major bleeding complication is defined as bleeding related death, intracranial bleeding, intra-organ bleeding, surgical -, radiological—or endoscopic intervention related to bleeding or necessity of inotropic medication.

Secondary endpoints consists of non-major bleeding complications leading to early cessation of thrombolysis, other bleeding complications, and treatment related complications such as trash, compartment syndrome, 30 day re-intervention,30 day major amputation and non-bleeding related death. A list of all endpoint definitions is available in the (S2 File).

An independent clinical adjudication committee is constructed for the assessment of bleeding complications and consists of a trauma surgeon, haematologist and internal medicine physician. The committee will independently determine the presence of bleeding complications, its location and clinical implications with a standardized form and based on anonymized patient data. In this way, all relevant bleeding classifications for thrombolysis can be deducted and evaluated in a blinded fashion on their clinical implications. In case of disagreement between the three members, discrepancies will be discussed until unanimous decision (See Fig 1).

**Fig 1 pone.0302830.g001:**
[figure not shown]
The independent adjudication committee will define and score presence and severity of bleeding complications in a blinded fashion.

### Lab manual for blood samples

For the duration of CDT, simultaneous to standard procedures, venous blood samples will be collected every 6 hours consisting of an extra 6 ml EDTA and 4.5 ml Citrate tube, starting with the first blood collection before the enhancement of the CDT treatment (See Fig 2). When CDT stops, blood collections for the biobank will stop immediately. Venous blood collection is done by a second peripheral venous catheter which will not be used for fluid or medication administration. Blood samples are not collected by using the sheath or thrombolysis catheter, as thrombolytic medication might interfere with the coagulation biomarkers used for future analysis. Blood samples are centrifuged at 2000g for 10 minutes at room temperature and plasma is stored in 0.5ml tubes within two hours after collection at -80° C. These samples are then transported from participating centres to a central biobank of the University Medical Center Utrecht and again stored at -80° C awaiting future analysis (See Fig 3). All future analysis will be done in a single laboratory facility,

**Fig 2 pone.0302830.g002:**
[figure not shown]
Blood sample collection protocol.

**Fig 3 pone.0302830.g003:**
[figure not shown]
Processing of blood samples.

### Data collection

Data will be prospectively collected from electronic medical records and pseudo-anonymized by the study data manager. Only the data manager will have access to the pseudo-anonymisation key. Data regarding patient characteristics at presentation such as comorbidities, medication use, occlusion specifics and data of hospital admission and follow-up will all be collected and stored in the data management system Castor EDC. Pseudo-anonymized blood samples will be stored and analysed later by trained laboratory personnel. All laboratory outcome data will be digitally stored in a secured location at the University Medical Center Utrecht. The anonymized and encrypted data is only available for authorized research personnel. A list of all included variables is available in the (S3 File). See Fig 4 for a summary of the POCHET biobank.

**Fig 4 pone.0302830.g004:**
[figure not shown]
Summary of POCHET study.

### Patient and public involvement

Currently, in the explorative phase of the POCHET biobank we have chosen not to involve patients with the establishment of the biobank. But, when the POCHET biobank has stored blood samples of many different enrolled patients, the database can be used to contribute in a broad spectrum of research questions, for which both patient—or national cardiovascular associations can play a key role in formulating and designing future research.

### Statistical analysis

Baseline characteristics will be presented as mean ± standard deviation in case of normally distributed data and as median ± interquartile range for skewed data. Categorical variables will be stated as absolute numbers and percentages. Groups will be made according to bleeding or no bleeding complication during thrombolytic treatment and baseline characteristics will be compared using T-Tests, Wilcoxon Rank-sum test and Pearson’s Chi Square tests when applicable. The predictive value of different haemostatic components on bleeding complications will be analysed by regression analysis. The discriminative power will be measured by C-statistics and Net Reclassification Index. Univariate and Multivariate Cox Regression analysis will be used to test for predictors for bleeding complications, mortality and limb salvage. Proportional hazard assumption will be used to correct for competing interest.

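### The plan names the proportional hazards assumption as its correction for competing risks; it corrects nothing, so the planned Cox models carry no such correction

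*Protocol article*

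**What the plan says.** The Statistical analysis section assigns methods to three tasks.

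- Biomarkers: "The predictive value of different haemostatic components on bleeding complications will be analysed by regression analysis". The type of regression is not given. The next sentence reads "The discriminative power will be measured by C-statistics and Net Reclassification Index".
- Predictors: "Univariate and Multivariate Cox Regression analysis will be used to test for predictors for bleeding complications, mortality and limb salvage".
- Competing events: "Proportional hazard assumption will be used to correct for competing interest".

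The last sentence is all that the article says on competing events. It does not list which events compete, and it mentions no cumulative incidence function, set of cause-specific models or Fine-Gray model.

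Two other sections set the time frame. Endpoint definitions states "The primary endpoint is the occurrence of non-acces site related major bleeding during CDT", and its secondary endpoints include "non-major bleeding complications leading to early cessation of thrombolysis", non-bleeding death and 30-day major amputation. Study design limits the window: "With a maximum CDT-duration of 72 hours".

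**The concern.** Proportional hazards means that a covariate multiplies the hazard by the same factor at all times. The Cox model needs this condition in order to report a single hazard ratio. Whether or not it holds, it does not change how patients who die or stop CDT before bleeding enter the analysis. The sentence therefore names a tool that cannot do the job it is given.

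Competing events follow from the design. Because the primary endpoint counts only bleeding during CDT, a patient whose infusion ends can no longer have it. The 72-hour limit closes every patient's window. Early cessation for non-major bleeding and non-bleeding death are both foreseen as separate outcomes. For limb salvage, death removes the possibility of amputation.

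Two things are at stake. A reader would believe that competing risks had been handled when they had not. And if absolute risks were taken from a Cox or Kaplan-Meier fit with these events censored, they would describe patients kept on infusion for the full 72 hours, not patients as treated. A Net Reclassification Index in its usual forms is built on predicted risks and would inherit the error.

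**Working it through.** The article states no absolute risk, event count or power figure for this point, so there is no figure to reproduce. The check asks how far a naive risk could depart from the true one.

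**Inputs**

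- Bleeding risk pb = 9%. The Introduction gives an average bleeding rate of 18%, almost half of it major: 0.18 × 0.5 = 0.09. This covers all major bleeding. The primary endpoint excludes access-site bleeding, so its risk may be lower.
- Window: 72 hours (Study design).
- Probability pc that a competing event comes before bleeding: not in the article. Assumed range 1% to 80%.
- Constant cause-specific hazards over the window: assumed.

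**Formulas**

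- Total cumulative hazard: L = −ln(1 − pb − pc)
- Bleeding share: Lb = L × pb / (pb + pc)
- Naive risk with competing events censored: 1 − exp(−Lb)
- True cumulative incidence: pb

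**One case in full**, pc = 40%: L = −ln(0.51) = 0.6733. Lb = 0.6733 × 0.09/0.49 = 0.1237. Naive risk = 1 − exp(−0.1237) = 11.6%, against a true 9%.

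| Competing event first (assumed) | Naive risk | Ratio to true 9% |
|---|---|---|
| 1% | 9.05% | 1.005 |
| 2% | 9.1% | 1.010 |
| 5% | 9.2% | 1.027 |
| 10% | 9.5% | 1.056 |
| 20% | 10.1% | 1.120 |
| 40% | 11.6% | 1.293 |
| 60% | 14.2% | 1.574 |
| 80% | 20.0% | 2.223 |

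The rows from 1% to 5% represent death within 72 hours as the only competing event. The rows from 40% to 80% represent end of CDT being censored.

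**Relative effects.** Suppose a marker doubles the bleeding hazard.

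- If it leaves the competing hazard alone, the approximate subdistribution hazard ratio, ln(1 − CIF₁)/ln(1 − CIF₀), is 1.97 to 2.00 for pc between 2% and 60%, close to the cause-specific value of 2.
- If it also doubles the competing hazard, the ratio falls to 1.98 (pc = 2%), 1.77 (20%) and 1.33 (60%).

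The cause-specific ratio is 2 throughout. It remains a valid measure of association with the bleeding hazard. What it does not give on its own is the effect on absolute risk.

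**The case against.** A reader might infer that the bleeding rates and predictions from this biobank will be wrong. The article does not support that.

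- It plans no Kaplan-Meier curve and no Cox baseline risk. Categorical data are to be given as counts and percentages, and patients are grouped by whether they bled during treatment. The natural estimate of the bleeding rate is a crude proportion over at most 72 hours. If every patient is followed to the end of CDT, the Aalen-Johansen estimate at 72 hours equals that proportion.
- Cox regression is planned for testing predictors. With competing events censored it estimates cause-specific hazard ratios, which suit that aim.
- A C-statistic depends on ranks, so uniformly inflated risks do not raise it. Only the Net Reclassification Index is exposed, and only if its risks come from Cox. Biomarker prediction is assigned to an unspecified regression, which could be logistic.
- A claim that risks would double or more needs assumed CDT durations and a 72-hour estimate that nobody has planned.
- The article says that some non-major bleeding leads to early cessation. It does not say that access-site bleeding stops CDT.

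All of this stands, and it limits the consequence. It could also be said that competing-risk detail belongs in an analysis plan, and that each research question needs its own ethics approval before samples are analysed, which leaves room to specify methods later. That would excuse silence. It does not excuse naming a method that cannot work. Reading the phrase as competing risks is an inference, but no other meaning fits directly after the Cox sentence.

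**Conclusion.** The sentence is wrong as written and should be changed. As the plan stands, the Cox models for bleeding during CDT and for limb salvage have no competing-risk correction, although the plan says they do.

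The effect on results is conditional. Predictor tests based on cause-specific hazard ratios are sound. Absolute risks and a risk-based Net Reclassification Index may be overstated if they are derived with death or end of CDT censored. On a true risk of 9%, the relative overstatement is about 0.5% to 3% (at most about 0.25 percentage points) if only death competes, and about 29% to 122% if end of CDT is censored in 40% to 80% of patients. These ranges rest on assumed competing-event rates and constant hazards. The 9% is the article's figure for all major bleeding, not for the narrower primary endpoint.

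This is a point that should be fixed. It does not by itself invalidate the planned analyses.

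**What to change.** Replace the sentence with wording that does four things:

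1. Names the competing events: death and end of CDT for other reasons, for bleeding during CDT; death, for limb salvage.
2. States that predictor effects will be estimated with cause-specific Cox models.
3. States that absolute risks, and any Net Reclassification Index based on them, will come from the cumulative incidence (Aalen-Johansen, Fine-Gray or combined cause-specific models), or from the crude proportion or logistic regression over the fully observed CDT period.
4. States separately that the proportional hazards assumption will be checked.

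This is one paragraph of text and slightly more analysis work. Settling it before the first biomarker assessments, planned at 100 inclusions, avoids choosing the method after seeing data. It needs the time and reason of each end of CDT; the variable list (S3 File) was not available here, so whether these are recorded should be confirmed.

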## Discussion

POCHET is the first large scale prospective biobank including patients with ALI undergoing CDT treatment. By prospectively collecting data from patients and obtaining sequential blood samples, it is possible to provide contemporary characteristics and outcomes of nowadays ALI-patients undergoing CDT and investigate the role of potential (new) biomarkers to predict major bleeding complications during CDT for ALI.

The assessment of new biomarkers to predict bleeding complications requires a uniform definition of a bleeding complication, classification in major or minor and access versus non access related bleeding complications. Although multiple bleeding classifications are available, none are specifically appropriate for CDT in ALI because they are derived from non-surgical cohorts and differ when calling a bleeding complication major [13–16]. The international society of thrombosis and haemostasis (ISTH), for instance, considers a drop of haemoglobin of 1,24 mmol/L (2g/dL) related to haemorrhage a major bleeding, although this might not have any clinical consequence to the CDT therapy [16]. Other bleeding classifications like the Thrombolysis In Myocardial Infarction (TIMI) and Bleeding Academic Research Consortium (BARC) are developed in patients with cardiac diseases and anti-coagulation therapies and thereby not reflecting patients with ALI [13,14]. The Clavien-Dindo classification, although widely used among surgical patients, is a very well defined grading classification for complications in general, but not specific for bleeding complications [17]. Therefore, an independent adjudication committee is implemented to this study, to assess bleeding complications from a basic clinical perspective such as bleeding location, haemoglobin drop, therapy needed and the necessity to seize thrombolytic therapy. In this way, bleeding complications are descriptive and different existing bleeding classifications can be deducted separately. Furthermore, for the definition of the primary endpoint of this study, non-access site related major bleeding complication, the commonly used criterion “necessity of transfusion of 2 or more units of blood” is intentionally not used as it is highly linked to the type of surgery or intervention in the surgical population [18]. A criterion covering events of excessive and unexpected blood loss are marked with the type of intervention that was implemented. That is why these events were incorporated in the definition of major bleeding complication for the POCHET trial, such as re-intervention. Nevertheless, blood transfusion in relation to any bleeding complication is relevant information and will be collected. With this information, different bleeding classifications can then be analysed for which classification is most clinically relevant for the population of patients receiving CDT.

The POCHET biobank has a broad scope of future research that can be conducted with the available samples and data. With an aligned thrombolytic therapy for every patient, existing risk factors for bleeding complications can be verified. Obviously, the usefulness of fibrinogen catches the eye as one of the first research questions to be answered when trying to end the debate on this matter, as its absolute value or degradation speed remains unproven in the prediction of bleeding complications during CDT [9,19,20]. Furthermore, clinical risk factors for bleeding complications, such as an older age, cardiac history, limb sensibility and/or motor deficit on presentation, platelet count, and occluded synthetic grafts, can be verified with this biobank [21,22].

Several potential biomarkers could be hold promise as a predictor for major bleeding during CDT. For instance Von Willebrand Factor (VWF), the platelet adhesion protein. VWF-platelet complexes are heavily degraded in tissue plasminogen activator therapy, such as alteplase, leading to fibrinolysis [23]. The subsequent inability for thrombus formation by plasminogen activation elsewhere can thereby lead to bleeding complications [24].

Furthermore, anti-plasmin and plasminogen activator inhibitor both serve as the main down regulators in fibrinolysis. These regulators must be surmounted during thrombolytic therapy around the thrombus for effective lysis, but still be effective in systemic circulation to avoid bleeding [25]. Low baseline levels before CDT or degradation of these down regulators during treatment might lead to bleeding complications.

Another promising marker is D-dimer, a major fibrin degradation product that is released upon cleavage of crosslinked fibrin by plasmin. Widely used in the screening for embolic disease such as deep venous thrombosis, a recent review showed potential prognostic value for D-dimer on safety and outcome in thrombolysis [26].

A recent addition in biomarkers are the proteins in plasma extra-cellular vesicles (EVs), bilayer lipid membrane particles excreted by each cell, containing important information concerning coagulation [27]. For instance, platelet-derived and red blood cell-derived EVs both support factor XII dependent thrombin generation and thereby enhancing the coagulation cascade [28]. Degradation of these vesicles during CDT might impede coagulation and thereby increase the risk of bleeding.

Furthermore, fundamental human research on coagulation and fibrinolysis is possible with the POCHET biobank, with both samples within one individual patient prior to thrombolysis and samples on which the homeostasis is completely shifted towards anti-coagulation. For instance, little is known about the effect of lipoprotein Lp(a), a risk factor for atherosclerotic disease, and induced thrombolysis. One effect might be that Lp(a) may compete with plasminogen and thereby increase thrombolysis time [29]. With increased thrombolysis time with high levels of Lp(a), bleeding complications might be more frequent in these patients and merits further analysis.

In summary, POCHET will be the first large scale biobank collecting consecutive blood samples of patients with ALI that undergo CDT. Related to its design, POCHET will 1) help characterise the consecutive ALI population treated with CDT, 2) help identify novel biomarkers to predict major bleeding complications and hence aid physicians and research scientists to create a safer thrombolytic therapy and 3) support a wide range of diverse research projects in the field of coagulation and related interventions.

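### If treating teams see fibrinogen and act on it, scoring an early stop as no bleeding during CDT biases its predictive value towards nil, and the stated competing-risk provision does not correct this

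*Protocol article*

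**What the plan says.** Fibrinogen is a headline question. The Abstract's Methods state: "Proposed biomarkers to be investigated include fibrinogen, to end the debate on its usefulness, anti-plasmin and D-Dimer". The Discussion repeats the aim, saying that "the usefulness of fibrinogen catches the eye as one of the first research questions to be answered when trying to end the debate", and names both the absolute value and the speed of degradation as unproven predictors.

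The outcome is confined to the treatment period: "The primary endpoint is the occurrence of non-acces site related major bleeding during CDT" (Endpoint definitions). The only endpoint that mentions stopping is "non-major bleeding complications leading to early cessation of thrombolysis". A stop prompted by a laboratory value has no category in the text shown.

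On analysis: "The predictive value of different haemostatic components on bleeding complications will be analysed by regression analysis" (Statistical analysis), with C-statistics and NRI for discrimination. Cox regression is also named. That section's closing sentence says the proportional hazards assumption will correct for competing interest, presumably meaning competing risks. The only adjustment named anywhere is for the thrombolytic agent (Study design).

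On visibility of fibrinogen, the Introduction says "plasma fibrinogen level (PFL) monitoring has been widely used to predict the occurrence of major bleeding complications", and also that the ESVS guideline does not recommend monitoring it routinely. Biobank blood is drawn "simultaneous to standard blood collection every six hours for the duration of thrombolysis", but the content of the routine draw is not given. Biobank assays are run later on stored plasma (Data collection).

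**The concern.** A marker that is visible during treatment can alter the outcome it is meant to predict. Suppose a value falls, the team ends the infusion, and no bleed follows. Follow-up for the primary endpoint ends at that moment, and a bleed/no-bleed regression counts the patient as a low-fibrinogen non-event. The marker is then charged with a false alarm that may have been a correct warning. Biobank sampling also ends with CDT (Lab manual for blood samples), so the fibrinogen course is cut short in the same patients.

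At stake is the reading of a null result. The study intends to settle whether fibrinogen is useful, and a null produced partly by clinicians responding to fibrinogen would not settle it. The first assessment comes at 100 inclusions, where a handful of bleeds decides the answer.

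**Working it through.** The article gives no figure on this point, so there is nothing to reproduce. The checks below show direction and size under stated assumptions.

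**Inputs from the article.** Average bleeding rate 18%, almost half major (Introduction): 0.18 × 0.5 = 9%. Expected major bleeds: 0.09 × 100 = 9 at the first assessment, 0.09 × 500 = 45 at the approved size. Sampling is six-hourly. Everything else below is assumed.

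**1. Closed form.** Let RR be the risk ratio (low versus not low) without marker-driven stops, and a the share of low-fibrinogen bleeds averted or moved outside the risk window by stopping. Then observed RR = RR × (1 − a), which reaches 1 at a = 1 − 1/RR.

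| RR | a at which observed RR = 1 |
|---|---|
| 2 | 0.50 |
| 3 | 0.67 |
| 4 | 0.75 |

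**2. Simulation, fibrinogen as a binary state.** Six-hour intervals, planned CDT of 24 to 48 h, about 34% ever low, bleeding calibrated to 9%, a given share stopped when first low. Patients are classed as ever low or never low, bleed or no bleed. The last column is the rate ratio with time-updated fibrinogen, censored at the stop.

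| True hazard ratio | Share stopped | RR | C | Time-updated, censored |
|---|---|---|---|---|
| 3 | 0% | 1.66 | 0.566 | 2.99 |
| 3 | 25% | 1.24 | 0.527 | 2.97 |
| 3 | 50% | 0.84 | 0.479 | 3.03 |
| 3 | 75% | 0.42 | 0.413 | 3.04 |
| 4 | 0% | 2.20 | 0.606 | 4.04 |
| 4 | 50% | 1.10 | 0.512 | 4.02 |

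The closed form fits: 1.66 × 0.75 = 1.25 and 1.66 × 0.50 = 0.83. The RR is below the hazard ratio even with no stops, because the ever-low grouping carries immortal time: a patient must stay on CDT long enough to become low. The early crossing of 1 in this table therefore owes something to a crude grouping as well as to the stops.

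In counts at 100 patients, hazard ratio 3: no stops gives 34.3 × 0.121 = 4.2 bleeds among the low and 65.7 × 0.073 = 4.8 among the rest. With half stopped, the low group has 34.3 × 0.061 = 2.1. About two bleeds separate an apparent association from none.

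**3. Simulation, continuous fibrinogen.** Baseline lognormal (median 3.5), decay rate lognormal (median 0.04/h, SD 0.6), mean CDT duration 24 h, hazard proportional to fibrinogen to the power −1.5, bleeding about 9% without stops. The trigger is 1 g/L at a six-hourly draw; it is illustrative only and not a proposed rule. About one third of patients fall below it.

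| Share stopped at first low value | C, speed of decline | Bleeding |
|---|---|---|
| 0% | 0.752 | 8.95% |
| 50% | 0.688 | 6.28% |
| 100% | 0.536 | 3.42% |

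Repeating this with other assumed spreads (27% ever low) gives C of 0.75, 0.74, 0.72, 0.69, 0.63 and 0.53 at 0, 10, 25, 50, 75 and 100% uptake. Baseline fibrinogen moves less: 0.58, 0.57 and 0.55 at 0, 50 and 100%. A censored (Harrell) C for speed is still 0.62 at 100%.

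**4. The stated remedy.** Proportional hazards is a condition on the Cox model: that the hazard ratio is constant over time. It does not determine how an event that ends the risk period is handled. In step 2 the bias is removed by censoring at the stop and updating fibrinogen over time, and the article specifies neither.

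**The case against.** The strongest objection is that the premise is not in the document. No passage says that a participating centre reports fibrinogen to the treating team or stops on it. The statement on wide use rests on a survey of general practice. The Abstract says guidelines recommend against using fibrinogen, and the Introduction says routine monitoring is not recommended. If no centre reports it, there is no effect. S1 or S3 may settle the matter, and an unstated censoring rule is commonly left to an analysis plan. All of this stands, and it makes the point conditional.

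Four stronger readings are tempting and not supported:

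- That teams acting on fibrinogen would prevent bleeding. This assumes that low fibrinogen marks risk and that stopping removes it, which is the question the biobank is meant to answer.
- That the plan defines its prediction analysis by a bleed/no-bleed split. The sentence "Groups will be made according to bleeding or no bleeding complication during thrombolytic treatment" introduces the comparison of baseline characteristics. Prediction is by regression and Cox models, and a properly specified Cox model could separate these stops.
- That newer markers would look better than fibrinogen for this reason alone. No calculation here includes a second marker. Markers that fall together with fibrinogen during lysis could be attenuated as well.
- That fibrinogen will look useless. In the continuous model it remains clearly predictive at 50% uptake.

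What survives is that the endpoint window is fixed as bleeding during CDT, and that the one provision the article states for competing events is not a method for them. That is a wrong statement in the text, not a detail left out.

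**Conclusion.** The point holds in conditional form. If fibrinogen results reach treating teams and influence when CDT is reduced or stopped, analyses that score those patients as free of bleeding are biased towards no association.

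The size depends on uptake. In the continuous model the C-statistic moves from 0.75 to 0.72 at 25% uptake and 0.69 at 50%, and approaches 0.5 only when nearly every team stops at the first low value. The association disappears sooner (between 25% and 50% for a hazard ratio of 3) only with a binary ever-low grouping and with every stop removing the bleed from the count. Trigger, uptake, hazard shape and CDT duration are all assumptions.

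Recovery of the true hazard ratio (2.97 to 3.04 for a true value of 3) assumes that stopping depends only on the measured fibrinogen and that enough low-fibrinogen patients continue CDT. At full uptake the second condition fails and the data cannot answer the question.

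**What to change.** 1. State whether fibrinogen is reported to treating teams during CDT, by centre.
2. Unless S3 already does so, record each fibrinogen value reported to the team, and the time and reason of every dose change and of the end of CDT, with laboratory value as one of the reasons.
3. Replace the sentence on the proportional hazards assumption with a cause-specific (or competing-risk) time-to-event analysis using time-updated fibrinogen. The end of CDT is censoring, and a stop triggered by a laboratory value is its own competing event. Compute discrimination in a form that respects this censoring, and say that it may still be attenuated.
4. Add a sensitivity analysis in patients or centres where fibrinogen was not reported to the team.
5. Word any negative conclusion on fibrinogen to match what steps 1 and 4 allow.

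The cost is two case-report-form items read from the medical record, one rewritten sentence and one sensitivity analysis. Inclusion is ongoing, so capture can begin now. The downside is that the unaffected subset may be small and the conclusion narrower. No change to clinical care is proposed.
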